### Interventions

We have developed a protocol intervention and manualized each intervention to increase internal validity. In the CBIA group, all participants will receive the same intervention content through a smartphone app. In the CBIA + TCC group, in addition to the aforementioned intervention, the intervention will be applied by psychologists (masters or doctoral-level degree) who will be trained for the administration of the intervention by two professionals with more than 20 years of experience in cognitive behavioral therapy. They will receive approximately 35 h of training consisting of theoretical and practical seminars and role-playing exercises. In this group, TCC sessions will be recorded. The professionals who will participate in therapists’ training will assess the degree of adherence to the manuals and the ability to apply the interventions, and will monitor the therapists weekly.

#### Cognitive-behavioral intervention administered through a smartphone app (CBIA)

We have adapted an indicated prevention intervention of depression based on the multifactorial model of Lewinsohn et al. [10] that has proved its efficacy in previous face-to-face studies [8, 9] and in conference telephone format [22] for application through a smartphone app. This cognitive behavioral intervention consists of five modules to be performed in approximately 5 weeks. In module 1, we will explain the concept of depression, the need for active coping with depressive symptoms, and we will train participants in diaphragmatic breathing, monitoring mood and self-reinforcing techniques. Module 2 will be focused on how pleasant activities affect mood and developing a plan for introducing such activities in the participants’ daily lives with the help of behavioral contracts. In module 3, we will address how thoughts affect mood and participants will be trained on techniques to manage thoughts. In module 4, we will explain how social contacts affect mood, give strategies for assertive communication, and encourage participants to increase their social contacts. In module 5, participants will review everything they have learned throughout the intervention and focus on relapse prevention.

#### Cognitive behavioral intervention administered through a smartphone app + telephone conference call (CBIA + TCC)

This group will receive, in addition to CBIA as described above, a telephone contact in group format (in groups of five caregivers approximately), using a conference system, for five weekly 30-min sessions. Group rules will be explained in the first session and positive or corrective feedback will be administered through the five sessions after revising the performed homework [18]. Positive feedback consists of providing information on the correct implementation of the intersessional tasks and reinforcement, and corrective feedback involves identifying those tasks that have not been adequately carried out and suggesting relevant changes to improve performance. We follow Miltenberg’s guidelines [18] to improve the effectiveness of feedback, namely that (1) it should be given immediately after the target behavior is performed; (2) it should contain praise or other reinforcement for doing the behavior correctly and, if the behavior is incorrect, some type of praise should be given for trying; (3) praise must be descriptive, focusing on how the behavior has been performed; (4) corrective feedback should not be negative and the performance of the participant should not be described as wrong or mistaken (it is better to focus on how to improve performance); (5) always praise some aspect of the behavior before providing corrective feedback; and (6) provide corrective feedback on one aspect of behavior at a time. Participants will also be encouraged to support each other in the process of change.

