### Randomization

Those participants who meet the eligibility criteria will be randomly assigned to one of the three conditions, CBIA, CBIA + TCC, or ACG, by a statistics expert not related to the study using a table of random numbers generated by a computer. The sequence of randomization will be communicated to the researchers by means of sealed numbered envelopes, one for each participant, with instructions to use them in numerical order. Due to the nature of the intervention, it is not possible to blind the participants for allocation status.

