### Statistical analyses

We will use the statistical package SPSS for Windows (version 21.0) for the analysis of the data. All analyses will be performed according to the intent-to-treat principle. If participants drop out from the study, the lost values ​​will be imputed using multiple imputation [33].

To analyze the incidence of depressive episodes in each of the measurement times (post-treatment, 1, 3, 6, and 12 months of follow-up), a global χ^2^ test will be performed to compare the three groups. If the differences are statistically significant (*p* < 0.05), pairwise comparisons will be performed using logistic regression. The relative risk and the required number of patients to be treated will be calculated following the formulas proposed by Guyatt et al. [34]. In addition, the time it will take participants to undergo a major depressive episode will be analyzed using a survival analysis. The analysis of the effect of the interventions on the outcome variable ‘depressive symptoms’ will be performed using two-way ANOVA with repeated measures. The analyses related to the effects of moderation or mediation will be carried out as per the recommendations of Baron and Kenny [35]. The model to evaluate moderation will include, as an independent variable, the type of treatment, the moderating potential, and the interaction between the two. An optimal combined moderator will also be sought according to Kraemer’s recommendations [36]. For the analysis of the mediation, we will perform adjustment of three regression equations to assess the effect (1) of the predictor variable (amount of treatment) on the dependent variable (change in depressive symptomatology after the intervention), (2) of the predictor variable in the mediator potential of the predictor variable (change in reinforcement and negative thoughts), and (3) of the mediator potential of the dependent variable, controlled by the predictor variable. Dropouts and adherence to interventions will be analyzed using a χ^2^ test to compare the percentage of dropouts and using an independent *t* test to compare the number of modules completed and the register of the intersessional tasks. Likewise, the level of satisfaction with the interventions will be assessed using the CSQ-8 through a frequency analysis and descriptive statistics, and both active conditions will be compared at post-treatment using an independent *t* test.

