On the other hand, this study proposes a possible solution to the problem of lack of adherence found in the existing tests of psychological interventions for the treatment of depression administered through an app [13, 14]. Specifically, we propose to complement the intervention program with group conference calls led by a therapist. In Internet-administered interventions, it has been found that adding regular telephone contact increases adherence substantially [41]. In addition, high levels of adherence to the intervention were found in a study [22] in which a cognitive behavioral intervention and a behavioral activation intervention applied by TCC, such as that proposed in this study, were conducted. In that study, average attendances were 4.6 and 4.2 of 5 sessions, respectively, and average completed homework assignments were 14.7 of 18 and 9.5 of 12. This study also showed a low percentage of dropouts (6.6%) at post-treatment, similar to that found at the same time point in a face-to-face intervention [8]. All this suggests that human contact is vital to achieve high levels of commitment to a non-face-to-face psychological intervention.

In addition, the fact that telephone contacts are grouped can save costs and introduce social support, the latter of which is an important strategy in behavior change [42]. Finally, the use of feedback as a psychological technique administered in these telephone contacts, following the guidelines recommended by Miltenberg [18], brings rigor and solidity to the intervention protocol, facilitates its replication, and reinforces the learning of the cognitive behavioral skills trained during the intervention, favoring the expected results.

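### Only the CBIA + TCC arm is treated in telephone groups, yet the tests that include it assume independent participants; if outcomes correlate within call groups, its standard errors are too small, mainly for secondary outcomes

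*Protocol article*

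**What the plan says.** Allocation is individual. The Randomization section passes the sequence to the researchers "by means of sealed numbered envelopes, one for each participant".

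Delivery then differs by arm. Under Interventions, "In the CBIA group, all participants will receive the same intervention content through a smartphone app", and the control arm also receives its material by app. The section on CBIA + TCC adds "a telephone contact in group format (in groups of five caregivers approximately" in weekly half-hour calls where homework is reviewed and feedback given, and it continues: "Participants will also be encouraged to support each other in the process of change". The Discussion describes the addition as a proposal to "complement the intervention program with group conference calls led by a therapist" and counts social support among the benefits of grouping.

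Statistical analyses names the tests. For major depression, "a global χ^2^ test will be performed to compare the three groups", and if that is significant "pairwise comparisons will be performed using logistic regression". Depressive symptoms (CES-D) go to a two-way repeated-measures ANOVA. Dropout is compared by chi-square and adherence by "using an independent *t* test to compare the number of modules completed and the register of the intersessional tasks". Satisfaction (CSQ-8) is compared between the two active arms by another independent t test. No term for call group or therapist appears.

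The Sample size section goes from 49 to 58 per group for attrition alone.

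**The concern.** Members of one call group share a therapist, hear each other's homework reviewed and are asked to help one another. Their outcomes may resemble each other more than those of members of different groups. This happens in one of the three arms only.

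The chi-square and t tests treat every person as a separate unit. Repeated-measures ANOVA allows for correlation within a person over time, not between people in the same call. If the within-group correlation is positive, the variance of the CBIA + TCC mean is understated. Comparisons of that arm with CBIA or control then give intervals that are too narrow and p-values that are too small.

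The exposure is greatest for secondary hypothesis 2 in the Background, that adding the calls improves adherence and satisfaction over the app alone. Those are the outcomes the group calls are meant to move, and the clustered arm is on one side of every such test.

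**Working it through.** **Inputs from the article.** 49 evaluable per group, 15% attrition, 58 randomized per group, an 18.6-point difference in incidence, two-sided α 0.05, power 0.80, call groups of about 5.

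**Assumed, because the article gives none.** ICC 0.02, 0.05, 0.10 and 0.15; for the primary outcome, incidence of 3.0% with intervention and 21.6% in control (21.6 − 3.0 = 18.6).

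**The plan's own figures.** 49 / 0.85 = 57.6, rounded up to 58; 3 × 58 = 174. Both reproduce. For the 49, the usual formula for two independent proportions at 3.0% vs 21.6% gives

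n = [1.96·√(2 × 0.123 × 0.877) + 0.842·√(0.0291 + 0.1693)]² / 0.186² = 47.7, so 48.

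At 3.5% vs 22.1% it gives 50. So 49 is reachable without a clustering term, although the arm rates are not stated.

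**Group size at analysis.** 58 / 5 = 11.6, so about 12 groups. After 15% loss a group of 5 averages 5 × 0.85 = 4.25 (equivalently 49 / 11.6 = 4.2).

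**Effect on a continuous outcome.** With m = 4.25:

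- design effect in the CBIA + TCC arm: DE = 1 + (m − 1) × ICC
- effective n = 49 / DE
- type I error of the unadjusted test against an unclustered arm of equal size: 2 × [1 − Φ(1.96 × √(2 / (1 + DE)))]

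| ICC | DE | Arm SE, true / naive (√DE) | Effective n | Type I error at nominal 5% |
|---|---|---|---|---|
| 0.02 | 1.07 | 1.03 | 46 | 5.4% |
| 0.05 | 1.16 | 1.08 | 42 | 5.9% |
| 0.10 | 1.33 | 1.15 | 37 | 6.9% |
| 0.15 | 1.49 | 1.22 | 33 | 7.9% |

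A simulation (58 in 12 groups, 9 lost at random, 49 in the other arm, 60,000 runs per ICC, ordinary t test) gave 5.4%, 6.1%, 6.9% and 8.0%, within 0.2 points of the formula.

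**Effect on the primary outcome.** At the assumed rates the CBIA + TCC arm contributes 0.03 × 0.97 = 0.0291 to the variance and the control arm 0.216 × 0.784 = 0.1693, a total of 0.1984. Only the first part is inflated. With full groups of 5, the less favourable case:

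- ICC 0.05, DE 1.20: √[(0.0291 × 1.20 + 0.1693) / 0.1984] = 1.015
- ICC 0.10, DE 1.40: √[(0.0291 × 1.40 + 0.1693) / 0.1984] = 1.029

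The standard error of the difference rises by about 1.5% to 3%. Power of a cluster-adjusted test is Φ[(0.186 − 1.96 × SE₀) / SE₁], with SE₀ = √[0.123 × 0.877 × (1 + DE) / 49] and SE₁ = √[(0.0291 × DE + 0.1693) / 49]. It is 0.810 without clustering, 0.779 at ICC 0.05 and 0.747 at ICC 0.10.

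**Events for a cluster-adjusted primary analysis.** 0.03 × 49 = 1.5, so one or two episodes in that arm spread over about 12 groups.

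**The case against.** The strongest reply is that the harm is conditional and modest. No ICC is given, and at 0.02 the error rate is 5.4% rather than 5%. Because allocation is individual, calls that had no effect on anyone would create no correlation, and the unadjusted test would keep its nominal size. Inflation arises only if the effect averages zero but differs between call groups. That is right, and the figures above carry this condition.

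Logistic regression can carry a cluster term, and the survival method is left open, so an analysis plan could deal with both. That too is fair. It does not cover the chi-square, ANOVA and t tests, which the article names in a form that assumes independence.

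A reader might infer that every test in the trial is invalid. The documents do not support that: CBIA versus control involves no call groups. Nor do they show that a handful of therapists led the calls, since the article gives no number. A reader might also conclude that the primary result is seriously compromised. At the assumed low event rate most of the variance lies in the unclustered control arm, so it is not.

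**Conclusion.** The point holds as a modest analysis fault, limited to comparisons that include CBIA + TCC. The structure is certain from the text: individual allocation, one arm treated in groups with intended mutual support, and named tests that ignore the grouping. The consequence depends on a positive ICC. The shared therapist and mutual support make one plausible, but the document does not quantify it.

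The secondary continuous outcomes carry most of the exposure, above all adherence and satisfaction between the two active arms. The result for primary incidence rests on the assumed 3.0% vs 21.6%; a higher event rate in the CBIA + TCC arm would give that arm a larger share of the variance and so a larger effect. The material is enough to ask for a change of analysis, but not to call the trial unsound or to demand a larger sample.

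**What to change.** - Record call-group and therapist identifiers for every CBIA + TCC participant while the calls are being delivered; they may be hard to reconstruct later.
- For CES-D, modules completed, intersessional tasks and CSQ-8, replace the ANOVA and t tests in comparisons involving CBIA + TCC with a partially nested mixed model. It should have a random intercept for call group in that arm only, each CBIA or control participant as a separate unit, and small-sample degrees of freedom. For CES-D, keep the within-person correlation over visits.
- For major depression incidence, keep the planned analysis and add a cluster-adjusted sensitivity analysis. Say in advance that it will be unstable with 10 to 12 groups and possibly one or two events in that arm.
- State under Sample size that 49 per group assumes no clustering.

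The cost is two data fields and some analysis wording. Intervals for comparisons involving CBIA + TCC become slightly wider. Allocation, delivery and recruitment do not change.

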#### Attention control group (ACG)

Participants in the control group will receive information on depression equal to the CBIA group in duration (five modules), extension, and mode of administration (via a smartphone app). Participants in this group will receive therapeutically inactive information about depression (e.g., what is depression, prevalence, causes, symptoms) and healthy habits.

### Outcomes

As shown in Table 1, we will collect information on the sociodemographic characteristics of caregivers and the care situation, major depressive episodes and other mental disorders, depressive symptoms, mediating variables (environmental reinforcement and negative thoughts), drop out, adherence, and satisfaction with the intervention. The self-administered instruments will be completed by the participants through the app. Hetero-administered instruments will be administered through the telephone by trained interviewers who will be blind to the objectives of the study, the interventions that will be administered, and the randomization to the different groups. The training of the evaluators will be carried out by two study researchers with more than 20 years of experience in evaluation, and will consist of 15 h of theoretical and practical seminars and role-playing about the measurement instruments and the evaluation strategies.

**Table 1 Tab1:** Overview of measures

Instrument	Format
Participant characteristics	
Sociodemographic and care situation characteristics	Self-administered
Primary outcome	
Major depression: SCID-5-CV	Hetero-administered
Secondary outcomes	
Depressive symptoms: CES-D	Self-administered
Reinforcement: EROS	Self-administered
Automatic negative thoughts: ATQ	Self-administered
Dropout and treatment adherence	Hetero-administered
Satisfaction with the service received: CSQ-8	Self-administered

*SCID-5-CV* Structured Clinical Interview for DSM-5 Disorders, Clinician Version, *CES-D* Center for Epidemiologic Studies Depression Scale, *EROS* Environmental Reward Observation Scale, *ATQ* Automatic Thoughts Questionnaire, *CSQ-8* Client Satisfaction Questionnaire

#### Sociodemographic characteristics and care situation

These will be evaluated through the Characteristics and Status of Caregiver Questionnaire used in previous studies [8, 9]. It records the sociodemographic characteristics of the non-professional caregivers (sex, age, marital status, social class, educational level, main activity) and the care situation (relationship with the person cared for, age and sex of the dependent, disease of the dependent, time caring for their relative and daily hours dedicated to the care).

#### Primary outcome measure: major depression

The presence of a major depressive episode will be evaluated with the Structured Clinical Interview for DSM-5^®^ – Clinician Version (SCID-5-CV; [23]). This provides diagnoses of DSM-5 and must be administered by a clinician. It includes the most common disorders in clinical practice, namely depressive disorder, bipolar disorder, schizophrenia and other psychotic disorders, substance use disorders, anxiety disorders, obsessive-compulsive disorder, post-traumatic stress disorder, attention deficit hyperactivity disorder, and adaptive disorders, and it allows the screening of 17 additional disorders. For the pre-treatment evaluation, the entire interview will be used, while in the following evaluations only the module corresponding to the major depressive episode will be used. This interview has been applied face-to-face and telephonically [24]. Interobserver reliability (Kappa) ranges from 0.70 to 1.00.

#### Secondary outcome measures

##### Depressive symptoms

Depressive symptoms will be evaluated through the CES-D self-report scale [25] (Spanish version of Vázquez et al. [20]). It is a 20-item scale in which individuals report the frequency with which they have experienced each symptom during the previous week. Each of the items is evaluated on a Likert scale of four response options, with a range from 0 (rarely or none of the time) to 3 (most of the time). The total score range expands from 0 to 60, where a higher score corresponds to a greater depressive symptomatology. The internal consistency ranges from 0.85 to 0.90, with the Spanish version having a consistency of 0.89.

##### Reinforcement

In order to evaluate the reinforcement of the environment we will use the self-reported Environmental Reward Observation Scale (EROS) [26] (Spanish version of Barraca and Pérez-Álvarez [27]). It consists of 10 items in which the participant evaluates the degree of positive reinforcement received contingently from their environment on a Likert scale ranging from 1 (strongly disagree) to 4 (strongly agree). The total score ranges from 10 to 40, with a higher score indicating greater positive reinforcement. The internal consistency of the Spanish version is 0.86.

##### Automatic negative thoughts

Negative automatic thoughts will be evaluated through the Automatic Thoughts Questionnaire (ATQ) [28] (Spanish version of Otero et al. [29]). This is a 30-item self-report questionnaire in which participants must indicate, for each item, the frequency with which they experienced a series of thoughts during the prior week, in a Likert scale ranging from 1 (never) to 5 (always). The total score range extends from 30 to 150, where a higher score indicates more negative thoughts. Its internal consistency is 0.96.

##### Dropout and treatment adherence

A record will be kept of the dropouts produced in each group throughout the study. In addition, in the interventions, a record of the number of modules completed and the fulfillment of the intersessional tasks by each caregiver will be made.

##### Satisfaction with the service received

The satisfaction of the participants with the service received once the interventions are completed will be evaluated with the Client Satisfaction Questionnaire (CSQ-8) [30] (Castilian Spanish version of Vázquez et al. [31]). It is a self-reported scale of eight items and four possible answers, with a score ranging from 8 to 32, where a higher score implies a greater satisfaction with the service received. Its internal consistency ranges from 0.80 to 0.93 [32], with the Spanish version having a consistency of 0.80.

### Data management

Personal data (identifying information) and clinical data will be stored separately. The participant files will be stored in numerical order in a safe place. They will be kept for 5 years after completion of the study. All data will be entered into a database, in which individuals cannot be identified. Range checks and consistency checks against data already stored in the database will be made. All evaluation instruments, audio recordings, and hardware related to the study data will be kept in locked cabinets. Access to study data will be restricted, with a password system that only researchers will know, used to control access. A backup of the original database (primary database) will be performed twice a month. All reports and publications derived from the study will be prepared in such a way that no individual can be identified.

